### Outcome measurements

Data will be collected on anthropometrics, sleep, glycemic parameters, diet, biomarkers, and physical activity in night workers. Table 1 represents an overview of the outcome measurements.

**Table 1 Tab1:** Research outcomes for the study protocol

Domain	Method of measurement	Parameters
Objective Sleep	Actigraphy	• Total Sleep Time (TST), Fragmentation index (FI), Wake after Sleep onset (WASO), mid-sleep • Sleep latency • Sleep efficiency
Subjective Sleep	Questionnaires	• Insomnia Severity Index (ISI) • Epworth Sleepiness Scale (ESS) • Pittsburgh Sleep Quality Index (PSQI) • Shift Work Disorder Questionnaire (SWD) • Circadian Type Inventory (CTI) • Chronotype
Blood Glucose Variability	Continuous glucose monitoring	• Time within ranges (hypoglycemic < 3.9 mmol/L, target 3.9–10 mmol/L or hyperglycemic > 10 mmol/L range) • Glycemic variability (coefficient of variation, CV) • Mean amplitude of glycemic excursions (MAGE) • Mean of daily differences (MODD)
Food intake	Food logging	• Diet quality measured by ‘Eetscore index’ Dutch healthy eating guidelines • Eating patterns: temporal distribution of energy intake from (macro)nutrients
Blood parameters	Concentrations of Biomarkers	• Glucose, insulin, HbA1c • Lipid profile: high-density lipoprotein (HDL), low-density lipoprotein (LDL), free fatty acids (FFA), triglycerides • Inflammatory markers: high sensitive C-reactive protein (hs-CRP), interferon-gamma (IFN-γ), Interleukin (IL)-6, adiponectin, leptin, Interferon gamma-induced protein 10 (IP-10) • Kidney Function: glomerular filtration rate (eGFR), creatinine • Liver function: aspartate aminotransferase (ASAT), alanine aminotransferase (ALAT), albumin, Gamma-glutamyl transferase (gGT) • Blood screen: hemoglobin (Hb), Hematocrit (Ht), mean corpuscular volume (MCV), leukocytes
Stress	Cortisol concentration and subjective questionnaire	• Hair cortisol concentrations • Perceived Stress Scale (PSS)
Alertness	Psychomotor Vigilance Test	• A 5-min validated psychomotor vigilance test recording reaction times (RT)
Phenflex *(only for NU)*	A mixed-meal challenge with blood samples (t0, t30, t60, t120, t240)	• Metabolic flexibility: dynamic response of glucose, insulin, free fatty acids (FFA), triglycerides, and cholesterol to the challenge • Inflammatory resilience: dynamic response of IL-6, IL-8, IL-10, tumor necrosis factor (TNF-α) to the challenge

### Primary endpoints

#### Quality and quantity of sleep

Participants will wear a lightweight combined actigraphy and accelerometer device (MotionWatch 8; CamNTech) on their non-dominant wrist for 14 days at T0, T1, and T2, to assess total sleep time (TST), Fragmentation Index (FI), wake after sleep onset (WASO), and mid-sleep. Actigraphy data will be supplemented with validated sleep questionnaires, measuring sleep quality (PSQI) [44], daytime sleepiness (ESS) [43], and insomnia (ISI) [42]. Follow-up measurements will only include the PSQI, ESS, and ISI (and not the actigraph). Additionally, participants will complete the Circadian Type Inventory (CTI) [49].

#### Continuous glucose patterns and food intake

Participants will wear a blinded CGM device (FreeStyle Libre Pro; Abbott) for 14 days at T0, T1, and T2. The CGM will measure glucose concentration in the interstitial fluid every minute, and readings are stored in 15-min intervals. CGM data will be used to calculate time within ranges (hypo-, hyperglycemic, or target ranges), glycemic variability, and intra- and inter-day differences. Participants will be asked to log their food intake for 3 days while working night shifts at T0, T1, and T2, using the mobile app “HowAmI” (TNO, the Netherlands, Version 1.1.34), in order to match food intake to CGM values. The HowAmI app uses the MyFatSecret database (Secret Industries Pty Ltd., Victoria, Australia) to record food intake and connects to a custom, parallel back-end database to record the time stamp for each meal. Additionally, participants will complete an index of diet quality, measured with the ‘Eetscore’ dietary assessment tool (developed by Wageningen University [50]) at T0, T2, and T3. The index is based on the Dutch Healthy Diet Index 2015.

### Secondary endpoints

#### Clinical biomarkers in blood

Blood levels of the following markers will be measured in all groups at T0, T2, and T3 from fasted blood samples: serum levels of glucose, insulin, HbA1c, lipid profile, kidney, liver function, blood screen, and inflammatory markers (for specifics, please see Table 1).

#### The PhenFlex Test

Participants in the NU group will drink the mixed-meal Phenflex Challenge Drink at T0 and T2. The Phenflex test is a beverage (440 ml) composed of lipids, carbohydrates, and protein corresponding to 950 kcal [51]. After an overnight fast, the beverage should be consumed in 5 to 15 min. Venous blood samples are collected via an intravenous cannula under fasting conditions (t = 0 min) and after ingestion of the PhenFlex drink (after 30, 60, 120, and 240 min). From the Phenflex test, it is possible to calculate metabolic and inflammatory resilience and to determine tissue-specific insulin resistance. Metabolic resilience is calculated from the dynamic measurements of glucose, insulin, free fatty acids (FFA), triglyceride (TG), and cholesterol, while inflammatory resilience is based on dynamic measurements of IL-6, -8, and -10, and Necrosis Factor Alpha (TNF-α).

### Anthropometrics

Anthropometric measurements will be done in all study groups at T0, T2, and T3 and include height (measured with Seca 213 Portable Height Measure), body weight (TANITA BC-730 or Seca 877 scale), and BMI. Hip- and waist circumference will be measured using measuring tape. Blood pressure will be measured using an automatic blood pressure monitor (e.g. Omron).

#### Objective and subjective alertness during night shifts

At T0, T1, and T2 participants will complete an alertness assessment involving a psychomotor vigilance task (PVT) on a mobile phone [52, 53], performed at the start and end of night shifts for 2 consecutive nights. The PVT is a visual reaction time (RT) test in which the participant is asked to maintain the fastest possible RTs to a simple visual stimulus [13, 54]. We will use a 5-min validated PVT which is suitable for the time-constrained environment of shift workers (NASA PVT + , USA, Version 1.2.0 or 1.4.4) [53] and training on the PVT during the baseline visit will minimize practice effects. Additionally, after completion of the PVT, sleepiness will be rated on the 9-point Karolinska Sleepiness Scale (KSS) [55].

#### Feeling of hunger, abdominal complaints, and faintness during night shifts

After the PVT during their night shifts, participants will complete a 6-item Visual Analog Scale (VAS) on hunger, fullness, desire to eat, thoughts of food, stomach upset, and feeling faint [23].

#### Stress markers

Hair cortisol reflects the cumulative secretion and long-term cortisol exposure. Therefore, we will cut a hair pluck of approximately 100 hairs from the posterior vertex of the scalp at T0, T2, and T3. Hair will be stored at room temperature in an envelope until analysis. Cortisol levels will be measured using an ISO 15189;2012-accredited LC–MS/MS method for hair cortisol analysis [56]. The method is described in detail elsewhere [57] and uses a Waters Xevo TQ-S system (Waters Corporation, Milford, MA, USA). Additionally, perceived stress will be assessed with the 4-item Perceived Stress Scale (PSS) [58] at T0, T2, and T3.

#### Quality of life

Quality of Life will be assessed with the WHOQOLBref questionnaire (26 items) at T0, T2, and T3, covering the dimensions life, health, energy, and personal satisfaction [59]. We will also examine work-life balance, via a 4-item validated questionnaire [60] at T0, T2, and T3.

### Covariates

#### Demographics

Information will be collected on age and sex at T0. Additionally, a comprehensive situation sketch will capture the social, work, and home environment at T0 (i.e. caregiver to a young child who sleeps/eats at certain times, very long commute to work, or very noisy neighborhood causing disrupted sleep). Lastly, participants will complete a one-item questionnaire [61] for chronotype (which is based upon the Munich ChronoType Questionnaire [62]) at T0.

#### Lifestyle habits

Self-reported information will be collected on smoking habits, average (weekly) alcohol intake, and medication use at T0 and T2.

#### Job characteristics

Participants will report on job type and work schedule (including deviations thereof) at T0, T1, and T2.

#### Subjective compliance with the intervention

Subjective compliance with the intervention will be assessed with a questionnaire in the SL and NU groups, during the intervention, after the intervention, and during the follow-up (to see if participants continued to use the advice after the intervention period ended).

### Statistical analysis

Our primary analysis will assess the changes over time (pre- and post-intervention) in sleep quantity, sleep quality and glucose regulation. The intra-individual differences within the NU and the SL group will be compared to the control group. By considering the intra-individual differences, participants can serve as their own controls, increasing the sensitivity of the analysis to potentially smaller changes.

Linear and logistic mixed models will be employed using statistical software (SPSS, R studio) to analyze the main effects over time for the factor condition (3 groups). A random intercept statement will account for inter-individual variations. Significance tests will be 2-tailed and at p ≤ 0.05. Covariates like age, sex, and BMI may be considered, and participants with baseline and at least one follow-up measurement will be included in the statistical analyses. Selective loss to follow-up will be analyzed through logistic regression. Covariates will be imputed using multiple imputation if needed.

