### Sample size calculations

Sample size calculations were employed in GLIMMPSE 3.0, a validated manualized sample size calculator for longitudinal designs [33, 34]. We performed a repeated measure analysis sample size calculation using the Hotteling-Lawley Trace statistic to test for a time-by-treatment interaction effect, aiming for a power of 0.80 and a Type I error rate of 0.05.

For sleep outcomes, we predict a standard deviation of 84.4 min for total sleep time (TST), based on a laboratory study [35] comparing a control group with a sleep intervention. These estimates are based on large effect sizes, and it is unclear how these scores translate to a field study, therefore a mean scale factor was included to account for alternative values. Furthermore, we assumed that the Pearson correlation between all time-points was relatively stable at 0.48 based on a study on TST with a 2-year interval [36] and preliminary data from an Erasmus MC study on sleep and corona vaccination in shift workers (unpublished data, for protocol, see S-CORE study [37]). Taken together, for a desired power of 0.80 and a Type I error rate of 0.05, we estimated that we would need 18 participants per group for a difference of 128 min in TST as the main outcome in the sleep intervention arm.

Due to the paucity of previous data on continuous glucose levels of shift workers, there is no clear notion of the expected variability in a representative population sample. However, there is one observational study [38] that compared 62 daytime workers to 62 night shift workers who wore a continuous glucose monitor for 3–7 days, which showed standard deviation of 0.49 mmol/L for a mean nighttime glucose of 5.32 [38]. We assumed Pearson correlations of 0.85 between T0 and T1 and 0.71 between T1 and T2, considering patterns observed in Type I diabetes patients [39]. With these assumptions, we calculated a required sample size of 25 participants per group for a difference of 0.23 mmol/L in continuous glucose measurements as main outcome in the nutritional intervention. In total, considering both CGM and TST, our required sample size is *N* = 25 per group.

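### The sample-size section rests on one main outcome per arm, but the primary-endpoint and analysis sections make 11 to 13 or more parameters primary, and the glucose mean that sets n = 25 is not among them

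*Protocol article*

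**What the plan says.** **Sample size calculations.** The section tests a time-by-treatment interaction, "aiming for a power of 0.80 and a Type I error rate of 0.05". It arrives at 18 per group "for a difference of 128 min in TST as the main outcome in the sleep intervention arm". For nutrition it arrives at 25 per group for a 0.23 mmol/L difference in continuous glucose. The standard deviation of 0.49 mmol/L belongs to a mean night-time glucose of 5.32.

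**Primary endpoints, sleep.** Actigraphy is used "to assess total sleep time (TST), Fragmentation Index (FI), wake after sleep onset (WASO), and mid-sleep". Three questionnaires (PSQI, ESS, ISI) supplement it, and the CTI is named in the same paragraph.

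**Primary endpoints, glucose.** "CGM data will be used to calculate time within ranges (hypo-, hyperglycemic, or target ranges), glycemic variability, and intra- and inter-day differences". The same subsection adds that "participants will complete an index of diet quality, measured with the ‘Eetscore’ dietary assessment tool".

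**Statistical analysis.** The primary analysis covers sleep quantity, sleep quality and glucose regulation, with no single variable named. Within-person changes in both active arms are compared with control, and "Significance tests will be 2-tailed and at p ≤ 0.05".

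**Elsewhere.** The Abstract gives the main outcomes broadly, as sleep measurements and interstitial glucose levels. The CGM row of Table 1 lists time in three ranges, coefficient of variation, MAGE and MODD, but no mean. The Introduction ties the sleep hypothesis to the sleep arm and the glucose hypothesis to the nutrition arm.

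**The concern.** A reader cannot tell which result would decide either hypothesis. The sizing implies one variable per arm, the endpoint section implies a long list, and the analysis section implies domains. Followed as written, the endpoint and analysis sections allow any of many parameters, nearly all of them unsized, to support a primary conclusion at 0.05. The 5% used in the sizing would then not describe the error rate of that conclusion.

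Two features sharpen this. PSQI, ESS and ISI are self-reports in an open-label study whose participants choose their arm, so they are the listed parameters most exposed to expectation. For mid-sleep, no direction of benefit is stated. Separately, the quantity that determined n = 25 is not among the CGM parameters that are to be derived, so the sized glucose test has no matching endpoint.

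**Working it through.** **1. The plan's own figure.** Inputs from Sample size calculations: difference 0.23, SD 0.49, correlations 0.85 (T0–T1) and 0.71 (T1–T2), alpha 0.05, power 0.80. The T0–T2 correlation is not given; I assume 0.71. With two groups, three time points and the same difference at T1 and T2, the Hotelling-Lawley test gives 79% power at 24 per group and 81% at 25. The stated 25 is reproduced, at an unadjusted 0.05 for a single outcome. It would be 28 at an assumed T0–T2 correlation of 0.60 and 16 at 0.85. The 18 per group for TST does not follow from the printed inputs alone (8 to 11). A scale factor is mentioned without its value and may explain this; it does not bear on the present point.

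**2. Count of primary parameters.**
- Actigraphy 4 (TST, FI, WASO, mid-sleep) + questionnaires 3 (PSQI, ESS, ISI) = 7.
- CGM: three ranges + variability + intra-day + inter-day = 6.
- Total 7 + 6 = 13. Counting the ranges as one gives 7 + 4 = 11. Adding CTI and Eetscore to 13 gives 15.
- Tests: 13 if each arm is tested on its own domain only; 13 × 2 = 26 if both arms are tested on everything.

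**3. Chance of at least one false-significant result with no true effect.**
Independent tests: 1 − 0.95^k. Counting only results that favour the intervention: 1 − 0.975^k.
Equal correlation ρ, with c = 1.96: 1 − ∫[Φ((c − √ρ·u)/√(1−ρ)) − Φ((−c − √ρ·u)/√(1−ρ))]^k φ(u) du. For the favourable direction the second Φ term is dropped. The documents give no correlations between parameters; ρ = 0.5 is an assumption.

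| Tests k | Either direction, independent | Either direction, ρ = 0.5 | Favourable, independent | Favourable, ρ = 0.5 |
|---|---|---|---|---|
| 13 | 49% | 33% | 28% | 17% |
| 26 | 74% | 48% | 48% | 24% |

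On the lower count, independent tests give 1 − 0.95^11 = 43% and 1 − 0.95^22 = 68%.

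**4. Sensitivity to the correlation structure.** With the sleep and glucose domains independent of each other, correlation 0.5 within each, and the shared control arm simulated, the either-direction figures are 39% (13 tests) and 60% (26 tests). Both lie inside the ranges above. At within-domain correlation 0.9 they fall to 21% and 35%.

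**5. One test per hypothesis.** 5% each; overall at most 0.05 + 0.05 = 10% (1 − 0.95² = 9.75% if independent).

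**6. Power cost of Holm for glucose.** Two time points, r = 0.85: SD of change = 0.49 × √(2 × 0.15) = 0.268. At n = 25, noncentrality = 0.23 / (0.268 × √(2/25)) = 3.03. Power is 84% at 0.05 and 76% at 0.025. At 0.025, 28 per group are needed for 80%.

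**The case against.** The strongest reply is that the sponsor has already chosen: the sample-size section names a main outcome per arm, the Introduction ties each hypothesis to one arm, and the questionnaires only supplement actigraphy. On that reading the overall risk is about 10%. Multiplicity rules are also commonly left to an analysis plan, and a journal article condenses. This stands in part: the absence of an adjustment rule is not the finding. What remains is that the choice made for sizing is not carried into the endpoint or analysis sections, and the glucose measure used for it is missing from the listed CGM parameters. Those are conflicts in what the article states.

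A reader might infer that a positive primary result is likely by chance alone. The documents do not support that. The figure exceeds one half only if all 26 tests count and correlations are low to moderate. It includes results favouring control; in the favourable direction every figure in the table is below one half. The three range percentages sum to 100%, so they are not three free tests. The own-arm reading, which fits the stated hypotheses, gives 33% to 49%.

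It is also fair that sleep quality belongs to the first hypothesis, so a sleep-quality measure could legitimately be primary if it were named and sized. Testing two different interventions separately at 0.05 is likewise defensible.

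**Conclusion.** The point holds as a conflict between sections. The trial is sized on one outcome per arm, while the endpoint and analysis sections give primary standing to 11 to 13 or more parameters at two-sided 0.05, and the mean glucose behind n = 25 is not a listed CGM parameter.

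If the broad set is followed, the error rate of a primary claim is several times the nominal 5%. The size depends on which tests count, on the direction counted, and on correlations that the documents do not give, so it should be reported as a range and not as a single probability. The defect can be corrected without changing data collection and should be corrected before outcome data are analysed; recruitment was still under way at submission.

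**What to change.** Reconcile the Abstract, Sample size calculations, Table 1, both Primary endpoints subsections and Statistical analysis:

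- Name one primary variable per hypothesis, matching the sizing: TST for sleep versus control, and mean (night-time) CGM glucose for nutrition versus control. Add the latter to Table 1 and the CGM subsection.
- Name one contrast for each. The sizing uses a time-by-treatment interaction, whereas the analysis section speaks of pre- to post-intervention change. Choosing a baseline-to-T2 contrast would be a new decision and not a restatement of the sizing.
- Make all other parameters secondary, reported as estimates with confidence intervals.
- State whether each intervention is tested separately at 0.05 or with Holm across the two.

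**Cost.** Mostly text, plus one derived CGM variable; no new measurements. The other parameters lose primary standing. Separate tests at 0.05 cost no power and leave the overall error at up to 10%. Holm holds it at 5%, but at its first step glucose power at n = 25 falls from about 84% to 76% (r = 0.85); if the TST test succeeds first, glucose is tested at the full 0.05. If a T0-to-T2 contrast is chosen, its correlation must be stated and the sizing rerun: at an assumed 0.71, glucose power at n = 25 is 57% at 0.05 and 45% at 0.025.

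### Requiring a follow-up measurement drops participants lost before their first follow-up, which can bias the between-arm change contrast if that early loss depends on baseline differently across arms

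*Protocol article*

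**What the plan says.** The protocol article, Statistical analysis, sets the analysis population by a positive rule: "participants with baseline and at least one follow-up measurement will be included in the statistical analyses". I read a follow-up measurement as any measurement after baseline.

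The same section plans linear and logistic mixed models "to analyze the main effects over time for the factor condition (3 groups"), and adds: "A random intercept statement will account for inter-individual variations". The target is a comparison of change: "The intra-individual differences within the NU and the SL group will be compared to the control group".

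Two sentences concern missing data. One is a check: "Selective loss to follow-up will be analyzed through logistic regression". The other covers covariates only: "Covariates will be imputed using multiple imputation if needed". Nothing is stated for missing outcomes beyond the mixed model and the inclusion rule.

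Sample size calculations rests on a time-by-treatment interaction, "aiming for a power of 0.80 and a Type I error rate of 0.05". Study design says that the groups are open-label and that participants may choose their intervention. Actigraphy and continuous glucose monitoring (CGM) are taken at T0, T1 and T2; fasting blood markers at T0, T2 and T3.

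**The concern.** A likelihood-based mixed model with baseline among the responses can use a participant who has only a baseline value. That value adds little precision, but it helps to estimate the arm's baseline mean in the group that was enrolled. This keeps the change estimate valid when early loss depends on the observed baseline.

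If such participants are removed first, the arm's baseline mean is that of the people who stayed. Suppose that those lost had low baseline values. The stayers then start too high and drift back towards the mean at follow-up, so their mean change contains regression to the mean. If this happens equally in every arm it cancels from the contrast. If it differs between arms, the remainder looks like a treatment effect or hides one.

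Unequal early loss is plausible here. Participants choose their arm, so baselines may differ, and the arms ask for different things: a personal advice meeting in both intervention arms, and a challenge test with blood sampling over 240 minutes in the nutrition arm only.

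**Working it through.** **Inputs from the document (Sample size calculations).** Total sleep time (TST): SD 84.4 min, correlation 0.48 between all time points, target difference 128 min. Glucose: SD 0.49 mmol/L, correlations 0.85 (T0 to T1) and 0.71 (T1 to T2), target difference 0.23 mmol/L, 25 per group.

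**Assumed inputs.** The document gives no dropout rate, no relation between dropout and baseline, and no T0 to T2 glucose correlation. All three are assumptions below.

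**1. The plan's own figure.** A change-score approximation at correlation 0.85 has SD of change 0.49 × √(2 × 0.15) = 0.268, so n = 2 × (1.96 + 0.84)² × 0.268² / 0.23² ≈ 21.4, or 22 per group. A Hotelling-Lawley calculation with two groups, T0, T1 and T2 all as repeated responses, an effect sustained at T1 and T2, and an assumed T0 to T2 correlation of 0.71 gives exactly the stated 25. With 0.60 or 0.85 it gives 28 or 16. The figure is therefore consistent with baseline as a repeated response, though this does not prove that the analysis will be built that way.

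**2. Size of the bias by formula.** Let a fraction p of one arm be lost before any follow-up, averaging k SD from the arm's baseline mean, with loss in the other arm unrelated to baseline. The stayers' baseline mean is displaced by [p/(1−p)] × k × SD. A fraction ρ of this carries over to follow-up, so the change contrast is off by

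bias = (1 − ρ) × [p/(1 − p)] × k × SD.

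With p = 0.2 and k = 1, p/(1−p) = 0.25:

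- TST, ρ = 0.48: 0.52 × 0.25 × 84.4 = 11.0 min; 11.0/128 = 9%.
- Glucose, ρ = 0.85 (documented, T0 to T1): 0.15 × 0.25 × 0.49 = 0.018; 8% of 0.23.
- Glucose, ρ = 0.71 (documented for T1 to T2, assumed for T0 to T2): 0.29 × 0.25 × 0.49 = 0.036; 15%.
- Glucose, ρ = 0.60 (assumed): 0.40 × 0.25 × 0.49 = 0.049; 21%.

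**3. Large-sample check.** A random-intercept model with a saturated group-by-time mean was fitted to 200,000 simulated participants per arm. Loss before T1 was logistic in baseline, with slope 1 per SD where baseline-dependent, and the T0 to T2 glucose correlation was 0.71. The entries are bias in the T0 to T2 change contrast, with the percentage of the target in brackets.

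| Early loss (control / intervention) | TST, rule applied | TST, all kept | Glucose, rule applied | Glucose, all kept |
|---|---|---|---|---|
| Same slope, 21% / 21% | 0.4 (0.3%) | 0.3 | 0.001 (0.3%) | 0.001 |
| Same slope, arms 0.5 SD apart at baseline | 2.7 (2%) | 0.1 | 0.009 (4%) | 0.002 |
| Baseline-dependent in one arm, 10% | 3.7 (3%) | −0.5 | 0.014 (6%) | 0.002 |
| Baseline-dependent in one arm, about 20% | 8.1 (6%) | 0.0 | 0.030 (13%) | 0.008 |
| Same slope, 10% / 31% | 7.5 (6%) | 0.4 | 0.023 (10%) | 0.003 |
| Opposite slopes, 21% / 21% | 16.0 (12.5%) | −0.1 | 0.052 (23%) | 0.008 |

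The sign reverses if low rather than high baseline values are lost. In the fourth row those lost lie 8.1 / (0.52 × 84.4 × 0.214/0.786) ≈ 0.68 SD from the mean, so k = 1 in step 2 is a stronger selection than the one simulated. The remaining 0.008 for glucose arises because a random intercept alone does not fit unequal correlations.

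**4. At 25 per arm (1000 runs).** With about 20% loss, baseline-dependent in one arm, TST bias was 6.9 min with the rule and −0.8 without it, with SD of the estimate about 27 min. For glucose it was 0.024 against 0.002, with SD about 0.12. When loss was completely random, the rule gained no precision: SD 26.7 with it and 26.0 without for TST, 0.116 and 0.114 for glucose.

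**5. Against sampling error.** 11.0/27 = 0.41 of a standard error for TST. For glucose, 0.049/0.12 = 0.41 at most; the 0.12 was simulated at correlation 0.71, and the standard error rises as the correlation falls. Only the opposite-slopes case goes above half, and only for TST (16.0/27 = 0.59).

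**The case against.** The strongest objection is that the article never says that baseline is a repeated outcome. Its target is intra-individual differences, and a participant without follow-up has none. If pure change scores are analysed, baseline-only participants cannot enter, the same bias arises, and the fix does not help. If baseline is a covariate they add nothing either; in the same simulations that analysis stayed at 127.6 to 128.4 min against a true 128 when the arms were equal at baseline. This objection stands as a condition on the point. It does not remove it, because the section names a mixed model over time and the sample size rests on a time-by-treatment interaction.

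Second, a reader might infer that the rule always biases the contrast, or that it discards all the protection of a mixed model. Neither is supported. The first row of the table shows essentially no bias when mechanism, rate and baseline are alike, even with 21% baseline-dependent loss. For actigraphy and CGM, anyone with T1 but no T2 stays in, so later loss is still covered.

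Third, a reader might take the planned logistic regression as a sign that the sponsor expects selective loss. It is a planned check, not a prediction. Nor is the control arm free of burden: the wearable devices are described for participants generally, and blood sampling for all groups. The advice meeting was kept light, and the second challenge test falls at T2, when those who reached T1 already have follow-up data.

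Finally, the effect is modest beside sampling error, and every dropout input is assumed. Both are true, and both limit the weight of the point.

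**Conclusion.** The point holds in a conditional form. With baseline in the response vector, the stated rule gives up validity under baseline-dependent loss before the first follow-up and brings no gain in return. It can bias the between-arm change contrast when the loss mechanism, loss rate or baseline level differs between arms.

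Under an assumed 20% early loss in one arm, with those lost 1 SD from the mean, the bias is about 11 min for TST and 0.018 to 0.049 mmol/L for glucose. That is 9% and 8 to 21% of the stated targets, and below half a standard error at 25 per arm. For blood markers, which are not measured at T1, the exposed group may be somewhat larger if the rule is applied outcome by outcome: it then includes anyone lost before T2 who does not return at T3.

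This is a minor improvement that costs nothing. It is not a flaw that threatens the trial's conclusions.

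**What to change.** Replace the inclusion rule with wording such as: *all enrolled participants with at least one measurement of the outcome, including those with baseline only, enter the likelihood-based mixed model, with baseline in the response vector.* This also settles the role of baseline, which the article leaves implicit. Keep the baseline-plus-follow-up set as a sensitivity analysis, and use the planned logistic regression on loss to follow-up to decide which further sensitivity analyses are needed.

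The cost is one sentence and one additional model run; no new data are needed. In none of the scenarios examined was keeping everyone materially worse. The change does not address loss that depends on unobserved outcomes, nor the confounding that comes from self-chosen arms. If the sponsor intends a baseline-covariate or pure change-score analysis, the article should say so, and this change then has no effect.
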